### Plans to promote participant retention and complete follow-up {18b}

#### Primary outcomes

MME will be retrieved from SDPR for participants who discontinue or deviate from the protocol.

#### Secondary outcomes

If the questionnaire is not returned within 3 weeks after being mailed, a telephone reminder will be performed. The follow-up visit will be scheduled at 4 and 8 months regardless of participants returning the SQRP questionnaire before the visit or not. If not completed before the visit, the participant will be given the opportunity to fill out the questionnaire at the time of the visit.

At 12 months, a telephone reminder will be performed if the questionnaire is not returned within 4 weeks. Hereafter, no further attempt is made to contact those who do not respond.

### Data management {19}

*Primary outcomes* are derived from the SDPR where all dispensed prescribed drugs are registered. The reliability of prescribed drugs at an individual level is good. Statistics are based on statutory reporting from pharmacies. Data collection is, to a vast extent automated, where data are extracted from administrative systems [51].

*Secondary outcome* data entry into SQRP is performed by medical staff according to standard clinical procedures at the department as they are part of the standard evaluation. A case report form is designed by SQRP’s Clinical Data Management team and it is used by all units reporting to SQRP. To secure validity, a tenth of the entry will be randomly checked. In case of discrepancies, all entries will be checked.

*Additional data* are transferred into electronic data capturing system, REDCap®, in accordance with a written case report form regarding information about self-report of opioid consumption the last week, allocation, date of written agreement, dates for visits, dates for follow-ups, frequency of contacts with the nurse, opioid-induced symptoms, structured interview of DSM-5 substance use disorder, drug screening, clinical assessment of substance use disorder, drop-offs, adverse events, global opinion about tapering effects on health, and review of medical records regarding opioid replacement therapy at 12 months.

### Confidentiality {27}

Data confidentiality will be protected in accordance with the routines of SDPR and SQRP. Additional data kept in REDCap® will be coded with study ID at each study center, and no other data providing personal identification will be kept. Linking of databases will be performed by the National Board of Health and Welfare.

### Plans for collection, laboratory evaluation, and storage of biological specimens for genetic or molecular analysis in this trial/future use {33}

Not applicable.

## Statistical methods

### Statistical methods for primary and secondary outcomes {20a}

All statistical analyses will be performed with the SPSS software (version 25, IBM Inc). Continuous data will be expressed by means, standard deviation and 95% confidence interval, and categorical data in numbers and percentages.

The intervention arm (tapering opioids) will be compared with control (waiting list) for primary and secondary outcomes at 4 months of follow-up. Statistical analysis of differences between groups will be performed per protocol (attending follow-up 4 months after the start of the intervention and attending second baseline visit in controls) with a paired *t*-test regarding the primary outcome and a Wilcoxon signed-rank test regarding secondary outcomes.

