### Trial design {8}

The design of the present study is an RCT, which is under recruitment and conducted among patients with long-term pain who have been accepted to undergo a structured intervention aiming to taper opioid long-term treatments. The study population will be randomly allocated to either (1) the start of tapering opioids immediately or (2) the control group who will return to usual care and commence tapering of opioids 4 months later. A 12-month follow-up after the start of the intervention is included (Fig. 1). The study lies within a superiority framework. Primary endpoints are hypothesized to generate a decrease in opioid use in comparison to controls.

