### Criteria for discontinuing or modifying allocated interventions {11b}

Non-compliance to the treatment plan or drug screening showing evidence of a drug not prescribed calls for attention from a physician. Additional screening for a multiple of drugs available on the illicit market may be performed. Renewal of the treatment plan is offered, and the participant may be retained in the study and final analysis.

If the treatment plan, despite this, is not followed, the participant is referred to an addiction care center and excluded from the final analysis.

There are no restrictions due to concomitant care and interventions during the trial.

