#### Primary outcomes

Consumption of opioids, measured as MME, will be evaluated using data extracted from the Swedish drug register of the National Board of Health and Welfare (SDPR) where registration of all withdrawals of prescribed drugs is made. MME will be calculated using these data. At all baseline visits and 12-month follow-ups, the MME will be calculated for the preceding 90 days, but at 4 months after the intervention, the dose will be calculated for the preceding 30 days as the intervention is estimated to last approximately 3 months.

Self-reported opioid consumption will also be evaluated and reported in MME. Calculation of morphine equivalent dose will be performed with conversion factors used in Cochrane review [7].

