## Data collection and management

### Plans for assessment and collection of outcomes {18a}

#### Primary outcomes

Individual data from the SDPR will be collected when all follow-ups are closed [51]. Self-report of daily opioid consumption at the time of the visit will also be assessed.

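### The only stated superiority comparison is per protocol and excludes persistent plan non-followers, although dispensed MME is retrieved for them; all randomised participants should form the primary set for that outcome

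*Protocol article*

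**What the plan says.** Trial design {8} states: "The study lies within a superiority framework". Statistical methods {20a} then gives the one between-arm comparison, at 4 months: "Statistical analysis of differences between groups will be performed per protocol (attending follow-up 4 months after the start of the intervention" in the tapering arm, and "attending second baseline visit in controls". No analysis of all randomised participants is stated for the primary outcome.

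Section {11b} first offers a participant who departs from the treatment plan a renewed plan and allows retention in the analysis. It continues: "If the treatment plan, despite this, is not followed, the participant is referred to an addiction care center and excluded from the final analysis".

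The primary outcome does not depend on attendance. Under Outcomes {12} it comes from the national drug register, where "registration of all withdrawals of prescribed drugs is made". Section {18b} adds: "MME will be retrieved from SDPR for participants who discontinue or deviate from the protocol". Self-reported consumption, also listed under primary outcomes, is different. Section {18a} says: "Self-report of daily opioid consumption at the time of the visit will also be assessed".

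The section on opioid replacement therapy states that this treatment is absent from the register and is taken from medical records at 12 months after the intervention.

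**The concern.** Attending the month-4 visit and keeping to the treatment plan both happen after randomisation and can depend on how the taper is going. A superiority comparison limited by them no longer compares the groups that were randomised.

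The plan exclusion is also lopsided. Controls return to usual care and start tapering 4 months later, so before the comparison they have essentially no taper to fail. People excluded for persistently not following a taper are probably those whose dose fell least. Removing them from one arm would make tapering look better than the effect of offering it.

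At stake are the between-arm difference in dispensed MME and the research hypothesis in Objectives {7} of a reduction of at least 50%. The protocol commits to retrieving the data that would avoid the problem, but gives them no stated use in the main comparison.

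**Working it through.** **Inputs from the protocol.** d = 0.5, power 80%, α = 0.05, drop-off 10%, 70 per group (Sample size {14}); allocation 1:1 (Sequence generation {16a}); reduction threshold 50% (Objectives {7}).

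**Inputs assumed.** The share f of taper patients excluded is not given. I show 10% (the protocol's drop-off figure), 20% and 30%. The outcomes of those excluded are also assumed, as stated in each step.

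**Step 1: the stated sample size.** n per arm = 2(1.960 + 0.842)²/0.5² = 62.8, rounded up to 63; 63/(1 − 0.10) = 70. This matches the protocol with a two-sided test. One-sided gives 50, then 56, which does not match. The sample size arithmetic is not at fault.

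**Step 2: size of the reduction.** Suppose analysed taper patients fall to 40% of baseline dose and excluded ones stay at 100%. Per protocol reports 1 − 0.40 = 60%. The all-randomised value is 1 − [(1 − f) × 0.40 + f × 1.00] = 0.60(1 − f). It drops below 50% once f exceeds 1 − 0.50/0.60 = 16.7%.

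**Step 3: standardised effect and power.** Suppose d = 0.5 is the per-protocol effect, excluded taper patients gain nothing over control, and the SD is unchanged. The all-randomised effect is 0.5(1 − f). Power with 70 per arm is Φ(d√(70/2) − 1.960).

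| f | Step 2: all-randomised reduction (per protocol 60%) | Step 3: all-randomised d (per protocol 0.50) | Per-protocol overstatement of d | Power, 70 per arm | n per arm for 80% |
|---|---|---|---|---|---|
| 10% | 54% | 0.45 | 11% | 76% | 78 |
| 20% | 48% | 0.40 | 25% | 66% | 99 |
| 30% | 42% | 0.35 | 43% | 54% | 129 |

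If d = 0.5 is instead already the all-randomised effect, power is Φ(0.5√35 − 1.960) = 84% with all 70 per arm, against Φ(0.5√31.5 − 1.960) = 80% with 63.

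**Step 4: type I error with no true effect.** Simulation with 20,000 runs, 70 per arm and normal outcomes with SD 1. A share f of the taper arm is removed according to a variable correlated with poor outcome; the same number of controls is removed at random. The test is two-sided at a nominal 5%.

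| f | Correlation with outcome | Shift toward tapering (SD) | Type I error |
|---|---|---|---|
| 10% | 0.3 | 0.06 | 6.3% |
| 10% | 0.5 | 0.10 | 8.8% |
| 20% | 0.3 | 0.11 | 9.1% |
| 20% | 0.5 | 0.17 | 15.6% |

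**The case against.** Four stronger readings are tempting, and the documents do not support them.

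- **That the analysis describes only people who succeeded in tapering.** It does not. The set is defined by attendance, and someone who attends with little or no reduction stays in. The 4-month visit section plans for participants still taking opioids, nurses may slow the taper, and {11b} offers a renewed plan before any exclusion.
- **That upward bias is established.** It is only the expected direction. An attendance condition applies in both arms, and selective non-attendance among controls could push either way. The protocol also does not say whether a control who fails the later taper is removed from the 4-month comparison.
- **That the false-positive rate would exceed 20%.** The simulation gives 22% at 10% excluded only if exactly the worst outcomes are removed, which is perfect selection. Similarly, the 50% hypothesis is missed at 20% excluded but not at 10%, the only rate the protocol gives.
- **That there is no data reason at all for the restriction.** This holds for dispensed MME only. Self-report and questionnaires cannot be recovered from the register for non-attenders. Replacement therapy is not in the register, and {11b} refers persistent non-followers to the kind of center that dispenses it. Register MME alone would make such patients look falsely low, again in favour of tapering.

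A separate analysis plan might add an all-randomised analysis. The protocol, however, positively fixes the comparison as per protocol and orders the exclusion, so this is a stated choice and not an omission.

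What stands of the objection limits the size and reach of the point and adds a condition to the remedy. It does not justify per protocol as the sole superiority analysis of dispensed MME.

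**Conclusion.** The point holds for dispensed MME at 4 months. A superiority trial should not rest solely on a set defined by attendance and adherence when the outcome is retrieved regardless of either. The likely direction favours tapering, on the assumption that plan non-followers reduced least and that attendance selection in controls does not offset this.

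The size cannot be computed from the documents. At the protocol's own 10%, and under the assumptions shown, the distortion is modest: 60% against 54% reduction, and a type I error of about 6–9%. At 20% it could change the conclusion on the 50% hypothesis (48%), with a type I error of about 9–16%. Because it bears on the primary conclusion and the remedy is cheap, it should be settled before the register data are extracted.

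**What to change.** 1. In {20a}, make the primary analysis of dispensed MME at 4 months include all randomised participants in their allocated arm, regardless of attendance or adherence. Fix the register window by date from randomisation, since a non-attender has no visit to count back from.
2. In {11b}, remove the exclusion from the final analysis for this outcome. The clinical steps there are not at issue.
3. Count opioid replacement therapy from medical records for the 4-month window as well, so that register MME is not read as complete for referred participants.
4. Keep the per-protocol comparison as a labelled supportive analysis.
5. In {14}, say whether d = 0.5 is the effect in all randomised or in the per-protocol set. In the first case 70 per arm gives about 84% power; in the second, if excluded patients gain nothing, about 76% at 10% excluded and 66% at 20%.

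Self-reported MME and the questionnaires for non-attenders lie outside this change.

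The cost is an amendment of wording and a short extra record check; the register extract is already planned for these participants. The estimated effect will probably be smaller, and if d = 0.5 was meant per protocol, power falls below the planned 80% at 10% excluded or more.

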## Interventions

### Explanation for the choice of comparators {6b}

It was considered non-ethical to deny patients interested in tapering of opioids the intervention. The study was therefore designed to use waiting list as the control group with a cross-over design receiving intervention after 4 months.

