### Sample size {14}

A “responder” to treatment is a participant who experiences at least a 50% reduction in opioid consumption [28]. Estimation of sample size was based on an effect size of 0.5 (Cohen’s *d*) 80% power, *α* = 0.05, and drop-off at 10%. The results from the calculation indicated the need for 70 individuals in each group.

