## Assignment of interventions: allocation

### Sequence generation {16a}

The allocation sequence is generated by computer to intervention or control in ratio 1:1 and is thereafter kept in sealed envelopes prepared by independent staff for an allocated group of 140 participants. Sealed envelopes will be kept in Lund and allocation will consequently take place in Lund.

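### The 4-month comparison between arms is assigned paired tests, although the two randomised arms are independent

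*Protocol article*

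**What the plan says.** Under *Statistical methods for primary and secondary outcomes {20a}*, the protocol article fixes the contrast: "The intervention arm (tapering opioids) will be compared with control (waiting list) for primary and secondary outcomes at 4 months of follow-up". It then says "Statistical analysis of differences between groups will be performed per protocol", and names the tests in the same sentence: "with a paired *t*-test regarding the primary outcome and a Wilcoxon signed-rank test regarding secondary outcomes".

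The design sections describe two separate sets of people. *Trial design {8}*: "The study population will be randomly allocated to either (1) the start of tapering opioids immediately or (2) the control group". *Sequence generation {16a}*: "The allocation sequence is generated by computer to intervention or control in ratio 1:1". No matching of participants is described. *Explanation for the choice of comparators {6b}* calls the trial "designed to use waiting list as the control group with a cross-over design receiving intervention after 4 months".

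*Sample size {14}* uses Cohen's d = 0.5, 80% power, α = 0.05 and 10% drop-off: "The results from the calculation indicated the need for 70 individuals in each group". It does not name a test.

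The only other inferential analysis described, under *Methods for additional analyses {20b}*, is a within-arm look at whether the tapered dose is maintained at 12 months.

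**The concern.** A paired t-test and a signed-rank test both work on differences within natural pairs. Across these two arms no such pairs exist. The stated purpose (a difference between groups) and the stated tests therefore cannot both stand.

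The superiority aim in *Objectives {7}* is at stake. If the paired tests are run in the way they can most naturally be run, as before-after tests within each arm, the result answers whether opioid use fell after baseline, not whether it fell more with tapering than with waiting. Any fall shared by both arms is then credited to the intervention. A shared fall is plausible here. Before randomisation every participant is told about opioid risks, and tapering is strongly suggested to those above 100 mg or on co-prescribed benzodiazepines (*Information to and screening of all participants before randomization*). Regression to the mean would act in the same direction in people referred because of their opioid use.

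**Working it through.** **1. What the sample size assumes.** Inputs from *Sample size {14}*: d = 0.5, power 80%, α = 0.05 (two-sided assumed, as sidedness is not stated), drop-off 10%.

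- Independent groups, normal approximation: n per arm = 2 × (1.960 + 0.842)² / 0.5² = 62.8, so 63. Inflated: 63 / 0.9 = 70. This is the stated figure exactly.
- Independent groups, t-based: 63.8, so 64; 64 / 0.9 = 71.1, so 72. Close to 70 but not exact.
- Independent groups, one-sided: 50, then 56. No match.
- Paired t-test at a standardised change of 0.5: 33.4, so 34 pairs; 34 / 0.9 = 37.8, so 38. No match.

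The stated 70 per group follows from a two-sided comparison of independent groups. That is an inference from the arithmetic, since the section names no test, but none of the other variants checked gives 70.

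**2. Whether the cross-over wording creates pairs.** Only controls change condition, and they do so after the 4-month contrast. A paired comparison of a control's waiting and tapering periods would be non-randomised, would leave out the intervention arm and is not what section {20a} describes.

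**3. Reading A: before-after tests within each arm.** Assume 63 evaluable per arm, normally distributed changes, no treatment effect, and a common mean change in both arms expressed in SDs of the change score. The documents give no figure for this common change, so a range is shown. Let p be the power of the paired t-test at n = 63. The arms are independent, so the chance that the intervention arm is significant and the control arm is not equals p(1 − p).

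| Common change (SD) | Intervention-arm test significant, p | Intervention significant, control not, p(1 − p) |
|---|---|---|
| 0 | 5% | 5% |
| 0.1 | 12% | 11% |
| 0.2 | 35% | 23% |
| 0.25 | 50% | 25% |
| 0.3 | 65% | 23% |
| 0.35 | 78% | 17% |
| 0.5 | 97% | 3% |

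The last column peaks at 25%, because p(1 − p) cannot exceed 0.25. A simulation with 20,000 runs at each of 0, 0.1, 0.2, 0.3 and 0.5 SD agrees to within about half a percentage point, and in it the independent-samples t-test stays at about 5% throughout.

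**4. Reading B: pairing participants arbitrarily across arms.** In the same simulation the type I error stays near 5% on average, but the answer depends on the order in which people are paired. In one simulated data set the independent-samples p-value was 0.049, while the paired p-value ran from 0.011 to 0.099 over 5,000 orderings. The test is undefined when the arms differ in size, which a per-protocol population makes likely.

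**5. What baseline adjustment would add.** With baseline-outcome correlation r, the effective effect size is 0.5 / √(1 − r²). With 63 per arm and a two-sided 5% t-test:

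| Assumed r | Effective d | Power |
|---|---|---|
| 0 (unadjusted) | 0.500 | 79.5% |
| 0.3 | 0.524 | 83% |
| 0.5 | 0.577 | 90% |
| 0.6 | 0.625 | 94% |

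The correlations are assumptions; the documents give none.

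**The case against.** The best defence is that this is a slip of naming. Section {20a} does commit to comparing the arms, the sample size fits an independent-groups test, and a fuller analysis plan may name suitable tests. All of this may be true. It does not remove the error, because the article does not leave the choice open: it fixes a test, and both the parametric and the non-parametric test it fixes are the paired versions. A slip needs the same correction.

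Parts of the defence do stand as limits on how far the point goes.

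- A reader might infer that the randomised contrast will never be validly tested. The documents do not support that. They show only that no suitable test is named in this article; an analysis plan not seen here may differ.
- A reader might infer that the superiority claim will certainly rest on within-arm tests. That is the natural way to run the named tests, but the protocol does not say so, and arbitrary pairing across arms is the other possibility.
- Counting every null trial in which the two arms disagree in significance gives up to 50%, but half of those have the control arm significant and the intervention arm not, which would not be read as superiority. The misleading direction is at most 25%.
- A reader might add that MME at 4 months will be skewed with many zeros. No distribution is given, so this cannot be held against the plan.
- The lack of baseline adjustment is not an error. An unadjusted independent-samples test would be valid, and covariates are commonly left to the analysis plan.

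**Conclusion.** The point holds and needs correcting before analysis. As written, the tests assigned to the difference between groups do not fit two independent, unmatched arms and do not validly test the superiority objective, and no independent-groups test is named in this document.

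The size of the consequence depends on how the sentence is carried out. As within-arm tests, false significance in the intervention arm ranges from 12% to 97% for assumed common changes of 0.1 to 0.5 SD, and the misleading split between arms reaches at most 25%, against a nominal 5%. As arbitrary pairing, the error rate is kept on average but the p-value is not reproducible. These figures rest on normal changes, 63 evaluable per arm and a common change that the documents do not quantify. The mismatch itself rests on none of these assumptions.

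The sample size is not wrong and does not change. The per-protocol population named in the same sentence is a separate matter.

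**What to change.** Replace the sentence naming the tests in section {20a} with an independent-groups comparison at 4 months.

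- **Primary outcome:** ANCOVA of 4-month MME on arm and baseline MME, reporting the adjusted mean difference with a 95% CI. An independent-samples t-test would also cure the error. The adjusted analysis is preferred because it gains power at no cost.
- **Secondary outcomes:** the same ANCOVA with the baseline score of each questionnaire, reporting a difference and 95% CI. A confidence interval also serves the non-inferiority aim in *Objectives {7}* better than a rank-test p-value alone.
- **Within-arm paired analysis:** keep it only for the 12-month retention question in section {20b}.

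The cost is a protocol amendment and a matching update to the registration, by the route in *Plans for communicating important protocol amendments {25}*. No new data are needed, since baseline MME and baseline questionnaires are already planned, and the target stays at 140. At publication 62 participants had been allocated, no interim analysis is planned, and register data are drawn only after all follow-ups close. Making the change before that extraction avoids choosing the primary test after seeing the data in an unblinded trial.

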### Methods for additional analyses (e.g., subgroup analyses) {20b}

#### Retention to intervention at 12 months

Analysis of retention to the tapered dose will be performed with a paired analysis within the allocated group. Changes in percent from the time point for follow-up after the received intervention at 4 months (intervention) or 8 months (control) will be calculated. The analysis will be performed with repeated measures ANOVA.

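### The 4-month comparison between two unmatched randomised arms is assigned a paired t-test and a signed-rank test, which do not fit the design; independent-groups tests should be named instead.

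*Protocol article*

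**What the plan says.** Protocol article, Statistical methods for primary and secondary outcomes {20a}, sets the contrast: "The intervention arm (tapering opioids) will be compared with control (waiting list) for primary and secondary outcomes at 4 months of follow-up". It continues: "Statistical analysis of differences between groups will be performed per protocol". The tests it then names for those differences are a "paired *t*-test regarding the primary outcome and a Wilcoxon signed-rank test regarding secondary outcomes". The analysis set is made up of tapering participants who attend the 4-month follow-up and controls who attend their second baseline visit.

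Four other places bear on this:

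- Sequence generation {16a}: "The allocation sequence is generated by computer to intervention or control in ratio 1:1". Neither this section nor any other in the article describes matching or pairing.
- Trial design {8}: the comparator is "the control group who will return to usual care and commence tapering of opioids 4 months later". The section on the choice of comparators {6b} describes this as "waiting list as the control group with a cross-over design receiving intervention after 4 months".
- Methods for additional analyses {20b}, on 12-month retention: "Analysis of retention to the tapered dose will be performed with a paired analysis within the allocated group".
- Sample size {14}, from an effect size of 0.5, 80% power, alpha 0.05 and 10% drop-off: "The results from the calculation indicated the need for 70 individuals in each group".

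**The concern.** A paired t-test and a signed-rank test work on differences within matched pairs. At month 4 the two arms are different people, allocated independently, and the numbers attending need not be equal. The sentence can be carried out in only two ways, and neither gives a sound comparison of the arms:

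- **Pairing across arms.** Someone has to decide which tapering participant sits beside which control, and nothing in the design settles that. If the arms differ in size, the surplus participants are lost.
- **Pairing within arms, baseline against 4 months.** Each arm is tested against itself. Nothing then tests the difference between the arms, although the primary objective claims superiority to control.

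The superiority claim on opioid dose and every 4-month result on pain, cognitions, mental health and quality of life rest on this one sentence. Controls begin tapering after month 4 and the 12-month analysis is within arm, so no later randomised comparison can stand in for it.

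**Working it through.** **1. Does the design supply pairs?** Allocation is individual and 1:1, with no matching. The cross-over is one-way: only controls have both a waiting period and a tapering period. A participant in the immediate arm has no waiting period and so supplies no pair. At month 4 the contrast is tapering participants against people still waiting.

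**2. Was a within-arm test meant?** The methods sentence says the differences are between groups. The 12-month section says within the allocated group when that is what is meant. The article therefore draws the distinction, and here it names the between-group contrast.

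**3. Reproduce the stated sample size.** Inputs from Sample size {14}: d = 0.5, power 80%, alpha 0.05, drop-off 10%. Sidedness is not stated; two-sided is assumed.

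- Independent groups, normal approximation: n = 2(1.96 + 0.842)²/0.5² = 62.8, so 63 per arm. 63/0.9 = 70, which is the stated figure.
- Independent groups, exact t: 63.8, so 64 per arm. 64/0.9 = 71.1, so 72.
- Paired t-test at d = 0.5: 33.4, so 34 pairs. 34/0.9 = 37.8, so 38.

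The stated 70 comes out of the independent-groups formula and is far from the paired one.

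**4. Pairing across arms.** Simulation with normal data and 63 per arm, pairs formed by arbitrary row order:

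| Quantity | Result |
|---|---|
| Type I error, no effect | about 5% (4.8% in one run) |
| Power at d = 0.5, arbitrary pairs | 79.3% |
| Power at d = 0.5, independent t-test | 79.7% |
| One arbitrary order disagrees with the independent t-test at 5%, d = 0.5 | about 3% of data sets |

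In a single simulated data set with an independent-test p of 0.17, reordering the rows 5,000 times moved the paired p from 0.04 to 0.26; the central 95% of orders gave 0.12 to 0.22. With 63 in one arm and 60 in the other, the paired test could not be computed.

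**5. Pairing within arms.** Suppose there is no tapering effect and both arms fall by the same amount, in SDs of the change score, with 63 per arm. Let p be the power of each within-arm test at two-sided 5%. The chance that tapering is significant and control is not equals p(1 − p), which cannot exceed 0.25.

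| Assumed shared fall | p | p(1 − p) |
|---|---|---|
| 0 SD | 5% | 4.8% (about 2.4% in the direction of a fall) |
| 0.1 SD | 12% | 11% |
| 0.25 SD | 50% | 25% |
| 0.5 SD | 97% | 2.5% |
| 0.75 SD | almost 100% | below 0.01% |

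A valid two-sided 5% test would falsely favour tapering in 2.5% of trials. The documents give neither the SD of change nor the expected drift in controls, so every shared-fall value above is an assumption.

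**The case against.** The best defence is that this is a naming slip: paired written for unpaired, signed-rank for rank-sum. The sample size supports that view. If the independent-groups tests are what will actually be run, neither harm above occurs.

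A reader might also draw three stronger conclusions that the documents do not support:

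- *The plan carries a 25% false-positive rate.* 25% is the mathematical maximum of p(1 − p). It is reached only near a shared fall of 0.25 SD, and only if superiority is read from two separate within-arm tests. The article gives no drift figure and does not say that it will read superiority this way.
- *Pairing across arms inflates error or makes results wildly unstable.* With equal arms the type I error stays at about 5% and power barely changes. In simulation, at least one of 200 row orders changed the 5% decision in 16% to 20% of data sets, but that counts the worst of many orders. For the single order an analyst would use, disagreement is about 3%.
- *The sample size proves an independent test was intended.* Sample size {14} names no test and no sidedness, and it opens by defining a responder. The exact t calculation gives 72, so 70 also depends on the normal approximation. The figure is consistent with an independent-groups design and inconsistent with 34 pairs; that is as far as it goes.

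What survives is that the published sentence names tests that do not fit the contrast. It is a wrong statement rather than a detail left for an analysis plan, and a valid analysis plan would have to contradict it.

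**Conclusion.** The point holds. The only randomised comparison in the trial is assigned tests that require pairs the design does not create. Across arms, the result is arbitrary in row order and undefined for unequal numbers, but error rates are close to nominal when the arms are equal. Within arms, there is no between-arm test, and an inference drawn from comparing two p-values would have a false-positive rate anywhere from near 0 to at most 25%.

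These sizes assume normal data, 63 analysable participants per arm, two-sided 5% testing and, for the within-arm figures, an equal change in both arms of unknown size. The finding itself depends on none of them; it follows from the article's own description of the allocation and the contrast. It should be corrected before the final analysis, because no blinding is planned for outcome assessment or data analysis and an unclear test leaves room for choice once the data are seen.

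**What to change.** In Statistical methods for primary and secondary outcomes {20a}, name one method for each type of outcome:

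- **Primary outcome:** an independent-samples (Welch) t-test of the 4-month value by allocated arm, reporting the mean difference with its 95% confidence interval.
- **Secondary outcomes:** the Wilcoxon rank-sum (Mann-Whitney) test by allocated arm.
- **Paired t-test and signed-rank test:** kept only to describe change within an arm.

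The cost is one sentence, with no new data. The primary sample size stands: 63 evaluable per arm gives 80.1% power by normal approximation and 79.5% by the exact t calculation. The Trial status section reports 62 of 140 participants allocated, so the change can be made well before the final analysis.
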